### Sample size calculation

The primary endpoint is the proportion of the study group who attend their diabetic retinopathy screening appointment. As the study group will comprise patients who have not attended screening for at least two years, including some who have never attended, despite previous interventions to encourage them to attend, this is a very hard to reach population. Attendance in the control group is expected to be extremely low, such as a nominal 1 %. As the eligible study population also tends to be the sickest, with the greatest risk of having retinopathy, and of losing their sight, even a small increase in attendance would have clinical and social benefit.

An increase in attendance of 10 % was deemed clinically significant. A 10 % increase was also considered achievable, as a study found that smoking cessation rates among employees of a large company increased from 5 % to 14.7 % with financial incentives [36], and in another study, warfarin adherence among subjects requiring anticoagulation management improved from 65 % to 97.8 % with a lottery based financial incentive [14]. With two intervention groups, each being compared to the control group, maximum statistical efficiency is achieved by randomising 1.4:1:1. Combining this with an assumed increase in attendance of 10 %, from 1 % in the control arm to 11 % in an intervention arm, there would be 95 % power if 1000 participants were recruited in total (412 in the control group, and 294 in each of the intervention groups). This sample size would also give the study at least 85 % power to detect a smaller increase from 1 % to 7.5 %, which would also be a clinically significant improvement in attendance rates. Should attendance in the control group turn out to be 5 %, the study would still have approximately 85 % power to detect an increase in attendance of 10 % to a level of 15 % in an intervention group [37].

Data from 1st Retinal Screen Ltd suggests that the study group could comprise over 1000 patients. This would allow oversampling at the randomisation stage, so that the intended sample size will still be reached even if participants become ineligible following randomisation (the most common reason for this is most likely to be due to participants attending their routine screening appointments).

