#### Pairwise comparisons

After summary statistics are analyzed, pairwise comparisons of success, or attendance, rates (absolute risk differences) will be performed between the following groups using Chi-square tests adjusting for multiple comparisons:Control vs. Fixed incentiveControl vs. Lottery incentiveFixed vs. Lottery incentive

Risk differences and risk ratios (i.e., relative risks), along with their 95 % confidence intervals, will be presented to assess whether any significant differences between groups exist. This analysis will address the first two research questions of whether financial incentives, and then the design of the incentive scheme have an impact on screening attendance.

Further analyses will be conducted to explore the third research question about whether the incentive schemes attract patients with a different socioeconomic or demographic status. Although groups will be checked after randomisation on the basis of demographic factors, an exploratory subgroup analysis will be performed for adjustment of treatment effect by accounting for the available demographic covariates listed above using a multivariate logistic regression analysis, and performing model selection using a backward stepwise removal process based on a 0.05 significance level; covariate-adjusted differences in success, or attendance, rates between treatment groups will be computed. Significant associations will be identified by those with *p*-values < 0.05, while possible trends toward significance will be identified from 0.05 ≤ *p*-values < 0.10. With anticipated relatively low success rates globally, resulting estimates from these subgroup analyses could be unstable [38, 39], hence affecting possible reliability of the estimates which is why we emphasize the *exploratory* subgroup analysis.

To answer the third research question, comparisons will also be made to those who are classified as regular ‘current’ attenders (i.e., those who have attended at least 2 appointments in the past 3 years) to assess possible differences through demographic covariates and secondary outcome data between regular attenders and non-attenders.

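### The stated 95% power (1% vs 11%) and approximately 85% power (5% vs 15%) do not follow from 412 vs 294 participants; both understate the power

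*Protocol article*

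**What the plan says.** The section Sample size calculation in the protocol article makes three power statements for one intervention arm against control, all at the same arm sizes.

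- Scenario 1, "from 1 % in the control arm to 11 % in an intervention arm": the article gives 95% "power if 1000 participants were recruited in total (412 in the control group, and 294 in each of the intervention groups").
- Scenario 2: "at least 85 % power to detect a smaller increase from 1 % to 7.5" per cent. This is worded as a minimum.
- Scenario 3, 5% vs 15%: "the study would still have approximately" 85% power.

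The split comes from the statement that "maximum statistical efficiency is achieved by randomising 1.4:1:1". Losses after randomisation are to be covered by oversampling, so 412 and 294 are the numbers intended for analysis. The section gives no alpha or sidedness. Under Pairwise comparisons, the three group contrasts are to be tested "using Chi-square tests adjusting for multiple comparisons", with no method of adjustment named.

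**The concern.** A rise from 1% to 11% with about 300 to 400 people per arm is a very large effect for that size, and 95% looks too low for it. Scenarios 1 and 3 share the same absolute difference and the same arms, so their powers should be linked through one alpha. A gap from 95% to about 85% has to be explained by the higher variance at 5% vs 15% alone.

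This paragraph is the article's only justification for 1000 participants, and it tells a reader what size of effect the trial could detect. If the powers are wrong, a reader will think the trial needed a gain of 6.5 to 10 percentage points to have good power, when a smaller gain would do. That matters here because the same section says that even a small increase in attendance would be worthwhile.

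**Working it through.** **Inputs.** Control n₀ = 412 and intervention n₁ = 294 (Sample size calculation). The split is right: 1000 × 1.4/3.4 = 411.8 and 1000/3.4 = 294.1. The rates are 1% vs 11%, 1% vs 7.5% and 5% vs 15%. Alpha and sidedness are not stated. I assume a two-sided test and show 0.05 to 0.05/3, the latter being a Bonferroni correction for the three planned contrasts. No deflation for dropout applies.

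**Formula.** Power = Φ[(p₁ − p₀ − z·s₀)/s₁], where

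- z = z(1 − α/2)
- s₀ = √[p̄(1 − p̄)(1/n₀ + 1/n₁)], with p̄ the weighted mean rate
- s₁ = √[p₀(1 − p₀)/n₀ + p₁(1 − p₁)/n₁]

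**Trying to reproduce the printed powers**

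Scenario 1 at 0.05: p̄ = 0.0516, s₀ = 0.01690, s₁ = 0.01890. (0.10 − 1.960 × 0.01690)/0.01890 = 3.54, so power is 99.98%.

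Scenario 3 at 0.05: p̄ = 0.0916, s₀ = 0.02203, s₁ = 0.02343. (0.10 − 1.960 × 0.02203)/0.02343 = 2.43, so power is 99.2%.

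| Scenario | Printed | α = 0.05 | α = 0.025 | α = 0.05/3 |
|---|---|---|---|---|
| 1% vs 11% | 95% | 99.98% | 99.95% | 99.9% |
| 1% vs 7.5% | at least 85% | 98.9% | 97.9% | 97.1% |
| 5% vs 15% | approximately 85% | 99.2% | 98.5% | 97.8% |

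The printed figures are not reproduced. Scenario 1 is about 5 points too low and scenario 3 about 13 to 14 points too low.

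**Other tests.** Exact enumeration of the Yates-corrected chi-square at 0.05/3 gives 99.99%, 97.9% and 97.8%. The unpooled, arcsine and continuity-corrected formulas also leave scenarios 1 and 3 more than 2 points from the printed values at these alphas.

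**Can one alpha give both figures?** Solving the pooled formula for alpha:

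- 95% in scenario 1 needs α ≈ 4.5 × 10⁻⁵, which leaves scenario 3 at 67% (and scenario 2 at 65%).
- 85% in scenario 3 needs α ≈ 5.9 × 10⁻⁴, which puts scenario 1 at 98.7%.

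With a tolerance of ±2 points on each printed power, the alpha ranges are 2.0 × 10⁻⁵ to 1.4 × 10⁻⁴ for scenario 1 and 4.2 × 10⁻⁴ to 8.3 × 10⁻⁴ for scenario 3. They do not overlap. The same holds for the unpooled, arcsine and continuity-corrected formulas.

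**Detectable rate at 412 vs 294, 85% power**

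| Control rate | Rate in the article | α = 0.05 | α = 0.05/3 |
|---|---|---|---|
| 1% | 7.5% | about 4.75% | about 5.5% |
| 5% | 15% | about 11.2% | about 12.2% |

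**Total needed for the printed powers.** Solve for n₀ with n₁ = n₀/1.4; the total is n₀ × 3.4/1.4.

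| Scenario and power | α = 0.05 | α = 0.05/3 |
|---|---|---|
| 1% vs 11%, 95% | about 412 | about 512 |
| 1% vs 7.5%, 85% | about 479 | about 622 |
| 5% vs 15%, 85% | about 455 | about 593 |

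The largest requirement governs: about 480 at 0.05 and about 620 at 0.05/3.

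**The case against.** The strongest reply is that the error does no harm. Power is understated, so every control comparison has more than the article promises, and the planned risk differences with 95% confidence intervals will carry the reading of a null result. This stands as a limit on the consequences. It does not make the figures right.

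A second reply is that the figures are floors. For scenario 2 this is correct: the wording is a minimum, and 97–99% meets it. Scenario 1 has no such wording, but suppose it is read that way too. At α = 0.001 the pooled powers are 99.1%, 86.2% and 88.0%, which meets both floors and comes within about 3 points of approximately 85%. That alpha is an implausible design choice and nothing in the article suggests it. At any usual alpha, scenario 3 is still wrong.

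A third reply is that the full protocol or an analysis plan may state alpha and the adjustment, and that the sizing method is cited to a source not at hand. So the absence of alpha from the article is not itself a fault. But no single alpha yields both printed powers, so supplying it would not repair them.

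A reader might also infer that 1000 is more than twice what the targets need. That holds only at unadjusted 0.05 (1000/479 ≈ 2.1). At 0.05/3 the ratio is 1000/622 ≈ 1.6. A reader might further fault the power for fixed vs lottery incentive, but the section claims no power for that contrast, and nothing in the article plans to read non-significance there as equivalence.

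**Conclusion.** The point holds for two of the three figures. The 95% for 1% vs 11% should be 99.9% or more, and the approximately 85% for 5% vs 15% should be 98–99%. The statement for 1% vs 7.5% is literally true but far below the actual 97–99%.

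These results assume a two-sided pooled two-proportion test with alpha between 0.05 and 0.05/3. That both figures cannot hold together does not depend on choosing alpha.

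It would be wrong to infer that the trial is underpowered, or that its randomisation, endpoint or test is affected. What is misstated is the detectable effect, and with it the link between the printed total and the printed powers. The cause cannot be determined from the article. A total of about 470 at α = 0.05 gives 97.0%, 84.5% and 86.1%, roughly the printed pattern, so a different total or an undisclosed input is possible.

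**What to change.** Keep 1000 participants. State the alpha, sidedness, multiplicity adjustment and formula behind the calculation, and recompute the three powers from them. As an illustration, at two-sided alpha from 0.05 down to 0.05/3 the text would give about 99.9% or more for 1% vs 11%, 97–99% for 1% vs 7.5% and 98–99% for 5% vs 15%. Add the matching minimum detectable effect: at 85% power from a 1% base, about 4.75% at 0.05 or 5.5% at 0.05/3. The level used should be the one the authors actually planned; the article does not specify Bonferroni over three contrasts.

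If an undisclosed input produced the printed figures, state it and reconcile the total with the powers.

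The cost is one corrected paragraph, with no change to recruitment, allocation or analysis.

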### Statistical analysis

#### Summary statistics

The primary outcome will be the count and proportion of attenders (i.e. attendance rate) by treatment group and demographics.

Secondary data will be the sight outcome scores from the screening test, aggregated by treatment group. This can be classified as disease compared to no disease, or sight outcome (annual recall, digital surveillance, refer to ophthalmology, refer to ophthalmology-urgent).

Those who become ineligible after randomisation and before receiving the invitation letter will be excluded from the analysis due to no longer meeting study inclusion criteria. However, a distribution of number becoming ineligible by treatment group, as well as reasons for ineligibility will be provided. Some participants may become ineligible after receiving the invitation letter, yet it can be assumed that the letter itself does not cause ineligibility, and so would occur at random across the experimental conditions. Therefore participants becoming ineligible after receiving the invitation letter will be excluded from the analysis.

The count and proportion of participants opting not to participate, or rearranging appointments, will be presented by reasons provided, as well as according to treatment group and demographics. If participants rearrange more than one appointment, they become ineligible for the incentive, and would be counted as a non-attender (even those in the control group). The count and proportion of participants who were classified as non-attenders for this reason will be provided, and they will also be included in a sensitivity analysis for comparison, where they will be classified as attenders.

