## Methods

### Study population and eligibility

Eligible participants will be identified from the Diabetic Eye Screening Programme (DES) prior to commencement of the study by 1st Retinal Screen Ltd (who at the time of the study were providing the DES service in the Kensington, Chelsea and Westminster Clinical Commissioning Groups in West London). Participants will be patients aged sixteen years and older, who have been invited to screening in the last 24 months on a yearly basis, but who have failed to attend or to have contacted the screening service to rearrange an appointment. A minimum two month period will be left between any of the standard invitation letters and enrolment into the trial to ensure that patients are not enrolled who are late to contact the screening service but who still intend to do so. Due to contractual requirements, the normal, annual invite process will continue for trial participants.

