**Fig. 1 Fig1:**
[figure not shown]
Flow diagram of study procedure. There will be oversampling at the randomisation stage, to allow for the sample size to be reached even if patients become ineligible between randomisation and the invitation letter being sent

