#### Control group

Participants in this group will receive the standard invitation letter from the Screening Service, which invites patients to a fixed appointment at a particular date and time (there is a number to call if patients need to rearrange their appointment). The letter will be sent four weeks before the appointment date.

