### Measures

The primary endpoint is the proportion of invitees who attend screening in each incentive group. This anonymised information will be extracted from the Screening Service database. For those participants who attend their screening appointment, data on their screening outcome score will be collected, aggregated by intervention group.

Demographic information will be collected for all invited participants on age, deprivation score and distance from screening center. Age data will given in deciles, starting from the lowest eligible age of 16 (i.e. 16–25, 26–35 etc.) with those aged 86 years and over being in the highest category. Deprivation scores will be measured based on the Indices of Multiple Deprivation score [35], which is based on postcodes, and will use the address to which the invitation is posted. This data will be given in deciles to ensure participant confidentiality. Distance to screening site will be measured based on the straight-line distance between the address on the day of screening, and the screening site, rounded to the nearest kilometre. Baseline demographics will also be collected for: gender, years registered, and years since last attended screening.

If participants telephone the screening center to opt not to participate in screening, the reason(s) provided will be recorded.

In all groups, when patients arrive, the screener will ask them for any reasons why they have not attended their past few appointments, in order to see if there are differences between intervention groups, and to explore common barriers to attendance in this hard-to-reach group. Reasons given will be noted in a table containing common reasons for non-attendance, along with the intervention group assignment. The reasons suggested are those given by patients in some informal telephone research conducted by 1st Retinal Screen Ltd (shown in Table 1).

**Table 1 Tab1:** Suggested reasons for past non-attendance

Suggested reasons for non-attendance	
Forgot	
Didn't know had an appointment	
Didn't get round to coming	
Was out of the country	
Started experiencing problem with eyes	
Did not feel obviously had problems with eyes	
Couldn't get time off work	
Didn't understand why needed to be screened	
Thought optician did it	
Family commitments	
Too ill to attend	
Seen privately	
Problems with transport	
Do not consider themselves diabetic	
Under the care of Hospital Eye Services	
Other - please specify	

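### Letter recipients who later become ineligible are dropped from the primary analysis on an untested assumption, although some may have been screened through the continuing routine service

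*Protocol article*

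**What the plan says.** Under Summary statistics, the protocol article treats ineligibility in two stages. People who become ineligible before receiving the letter are left out, with counts by arm and reasons to be reported. For those who become ineligible later, the rule is that "participants becoming ineligible after receiving the invitation letter will be excluded from the analysis". The reason given is "yet it can be assumed that the letter itself does not cause ineligibility, and so would occur at random across the experimental conditions".

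Four other statements bear on this rule:

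- Study population and eligibility: "the normal, annual invite process will continue for trial participants".
- Sample size calculation, on ineligibility following randomisation: "the most common reason for this is most likely to be due to participants attending their routine screening appointments".
- Measures: "The primary endpoint is the proportion of invitees who attend screening in each incentive group".
- Control group: "The letter will be sent four weeks before the appointment date". Study design and procedure also allows one rescheduling.

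The only sensitivity analysis on attendance status concerns people who rearrange more than once. None puts the post-letter exclusions back.

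**The concern.** The rule removes randomised people because of something that happens after the intervention has been delivered. That is harmless only if the event is unrelated to both arm and outcome, and the protocol assumes this without planning to check it.

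Its own text gives grounds for doubt. The routine route stays open after the trial letter, and using that route is a named reason for ineligibility. Someone who receives the trial letter and is then screened at a routine appointment has attended screening, which is the endpoint as Measures words it. Under the rule that person leaves both numerator and denominator.

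The arm may also influence the route. The incentive is tied to the trial appointment: the voucher expires on the screening date, the letter has to be brought along, and dedicated clinics are run for each group. Incentive recipients therefore have a reason to use the trial slot that controls lack.

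At stake is whether the primary comparison measures more people being screened or partly a shift in where they are screened. The cost per additional attendee and the Markov model take the same rates as input.

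**Working it through.** **Inputs from the protocol article.** Total 1000, ratio 1.4:1:1, planned attendance 1% control and 11% intervention (Sample size calculation); four weeks from letter to appointment (Control group). The number screened routinely after the letter is not given and is assumed below.

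**Group sizes reproduce.** 1000/3.4 = 294.1, so 294 per incentive arm and 1000 − 2 × 294 = 412 controls. Expected attenders are 0.01 × 412 = 4.1 controls and 0.11 × 294 = 32.3 per incentive arm. (The stated 95% power does not reproduce: the usual two-proportion formula gives 99.98% at an assumed two-sided 5% level. Nothing here rests on it.)

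**How many controls might be affected.** If routine slots were spread evenly over the year, about 4/52 × 412 = 31.7 controls would have one in the four-week window. At 1% attendance that is 0.3 people; at 5% it is 1.6. If every control had a slot in the window, 1% attendance gives 4.1. A plausible range is 0 to 4.

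**Effect at the planned rates.** Take 4 control and 32 incentive-arm attenders at the trial appointment. Let k further controls, and nobody in the incentive arm, be screened routinely after the letter.

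- Planned rule: control rate = 4/(412 − k).
- Any-route screening, all recipients: control rate = (4 + k)/412.
- Incentive arm in both: 32/294 = 10.88%.

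| k | Planned rule: control rate, RD, RR | Any route, all recipients: control rate, RD, RR |
|---|---|---|
| 0 | 0.97%, 9.91, 11.2 | 0.97%, 9.91, 11.2 |
| 1 | 0.97%, 9.91, 11.2 | 1.21%, 9.67, 9.0 |
| 2 | 0.98%, 9.91, 11.2 | 1.46%, 9.43, 7.5 |
| 4 | 0.98%, 9.90, 11.1 | 1.94%, 8.94, 5.6 |

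RD is the risk difference in percentage points and RR the risk ratio. Keeping all recipients but counting only the trial appointment gives the k = 0 row throughout (RD 9.91, RR 11.2). So the denominator alone moves little here. What matters is whether the k screenings are counted.

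**The direction can reverse.** Suppose 3 incentive recipients and no controls are screened routinely after the letter. The planned rule gives 32/291 = 11.00% against 0.97% (RD 10.03, RR 11.3). Any-route counting gives 35/294 = 11.90% (RD 10.93, RR 12.3). Here the exclusion understates the effect.

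**Equal loss is not neutral for the ratio.** With 5% of both arms screened routinely and trial-slot rates of 1% and 11%, the planned rule gives 1/95 = 1.05% and 11/95 = 11.58% (RD 10.5, RR 11.0). Any-route counting gives 6% and 16% (RD 10.0, RR 2.67).

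**Stress case with no true effect.** Let 5% of each arm be screened, with 4% of controls and none of the incentive arm through the routine route. The planned rule gives 1/96 = 1.04% against 5.00% (RD 4.0, RR 4.8), with about an 86% chance of p < 0.05. With 4% against 2% routine it gives 1.04% against 3.06%, and about 48%. These shares show what the rule permits; they lie well above the 0 to 4 people estimated above.

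**The case against.** The strongest reply is that the statement on routine screening explains oversampling, and the Fig. 1 caption ties oversampling to the period before the letter: "even if patients become ineligible between randomisation and the invitation letter being sent". No text says that routine attendance is the main reason for ineligibility after the letter. This stands. A reader might infer that the outcome itself decides who is excluded, but the documents support only that it may do so for some people.

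The window is also short, at least two months separate any standard letter from enrolment, and control attendance is expected to be about 1%. This stands too and limits the likely number of exclusions. The pairwise comparisons name absolute risk differences, which move by about one point or less in the 0 to 4 range.

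A reader might further infer that the rule favours the incentives. That needs more controls than incentive recipients to use the routine route, which is plausible but not documented. Nor does the article say who rules on ineligibility, so exclusion by unblinded staff cannot be asserted, and nothing shows that incentive recipients disclose more by telephone. The rule on people who rearrange more than once applies to all arms and has its own sensitivity analysis, so it is not part of this point.

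Finally, Sample size calculation words the endpoint as attendance at the appointment. Making any-route screening the sole primary definition would change that endpoint. This stands and shapes the fix. None of these replies justifies removing letter recipients on an assumption that is left unchecked.

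**Conclusion.** The point holds in a limited form. The plan fixes a post-letter exclusion that can depend on arm and on outcome, defends it by assumption, and plans no analysis that restores those removed. The article does not establish that such exclusions will be common or that they lean towards the incentives.

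If 1 to 4 controls were screened routinely after the letter and no incentive recipients were, the risk ratio at the planned rates would be about 11 under the plan, against 9.0 to 5.6 when all screening is counted. The risk difference would be 9.9 points against 9.7 to 8.9. The conclusion at a true effect of that size would not change. Larger differential shares could create an apparent effect, but they would have to be well above what the four-week window and 1% attendance suggest.

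**What to change.** - Make the primary analysis everyone sent a trial letter, in the arm assigned, with no post-letter exclusions. Exclusions before the letter can stay, because the letter cannot have influenced them.
- State in advance how routine screening after the letter is counted. On the full denominator, report both attendance at the trial appointment, which keeps the endpoint as worded in Sample size calculation, and screening by any route up to one cut-off common to all arms, as a pre-specified companion analysis.
- Report post-letter ineligibility by arm and reason.
- Keep the planned exclusion as a sensitivity analysis only.

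The cost is revised analysis wording and one extra field, the date of any screening after the letter, in the database extract already planned. Attendance rates will be slightly diluted by people who had moved or died, and any-route counting brings in attendances prompted by routine letters, which is why both versions should be shown.
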